### Outcome measures

#### Study participant-level outcomes

Each participant will be recruited at any point of IST care and will be assessed at baseline and at 9 months which reflects the time period an IST may be expected to be involved in working with a participant. This length of follow-up was chosen because our research and clinical experience indicates that, while there is a range of duration for IST involvement, assessment and delivery of behaviour support plans usually require about 3 months to complete and adults with ID and challenging behaviour often remain in the care of the IST for approximately 12 months.

The primary outcome is challenging behaviour measured by the Aberrant Behaviour Checklist-Community (ABC-C)^21^ which has been widely used in the target population and is completed by the caregiver (eg, family, paid care home staff, IST staff).

A range of secondary endpoints examine the following: the carer-reported Psychopathology Assessment for Adults with Developmental Disabilities checklist 22 is a mental health screening tool which provides sufficient information on potential mental health comorbidity that is often underascertained in adults with ID. The Threshold Assessment Grid^23^ measures clinical risk in adults with ID. The Quality of Life (QoL)^24^ will be used with the individual with ID and/or the caregiver, if participants lack capacity, to measure the individual’s quality of life. The Adaptive Behaviour Scale-Short Form assesses level of functioning.^25^ The Client Service Receipt Inventory (CSRI)^26^ (adapted for the study, 6-month retrospective service use at each assessment point) is a widely used service-use questionnaire and has been validated for use in mental health and ID services research.

Health-related quality of life will be measured by the EQ-5D-5L.^27^ The EQ-5D is used to generate quality-adjusted life years (QALYs). The self-report version will be used with the individual with ID where possible, and the proxy version will be used with the caregiver in the cases of participants lacking capacity.

The researchers will collect sociodemographic information, as well as number of hospital admissions and maintenance of accommodation at follow-up.

The study participant flow chart is shown in figure 1.

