#### Statistical analysis plan

As per the predetermined statistical analysis plan, the baseline characteristics of participants will be summarised separately for the two IST models. Categorical variables will be reported as counts and percentages, while continuous variables will be summarised as means and SDs or medians and IQRs as appropriate depending on the distribution of the data.

The primary outcome is challenging behaviour measured by total score on the ABC. Change in ABC total score from baseline to 9-month follow-up will be calculated for each participant. The mean difference in ABC score between the two IST models will be estimated from a multilevel linear regression model with change in ABC score as the outcome, a fixed effect of model as the main exposure, and a random effect of IST to account for clustering within services.

Age, gender, living arrangements, level of ID, level of risk, presence of autism and clinical comorbidities have been identified as potential confounders and will be specified as covariates in adjusted multilevel linear regression models similar to the main unadjusted model described above. The estimated difference in change in ABC total score from both unadjusted and adjusted models will be reported with accompanying 95% CI and p value.

The secondary outcomes detailed above will be analysed using statistical models analogous to those for the primary outcome. Binary outcomes will be analysed using multilevel logistic regression models. Non-normally distributed continuous outcomes will be analysed using the bootstrap method and bias corrected 95% CI will be reported. P values will not be reported for secondary outcomes.

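### Prior hospital admissions are not among the listed confounders for the non-randomised comparison of admissions, although the baseline service-use form may already record them

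*Protocol article*

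**What the plan says.** The section on study participant-level outcomes in the protocol article closes its list of measures by saying that the researchers will collect sociodemographic information "as well as number of hospital admissions and maintenance of accommodation at follow-up". No baseline count of admissions is named next to it. The same section describes the Client Service Receipt Inventory (CSRI) as "adapted for the study, 6-month retrospective service use at each assessment point". Participants "will be assessed at baseline and at 9 months", so one CSRI look-back covers the half-year before entry. On entry, the section says: "Each participant will be recruited at any point of IST care".

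The Statistical analysis plan section of the article fits, for the primary outcome, "a multilevel linear regression model with change in ABC score as the outcome, a fixed effect of model as the main exposure", with a random effect of IST. Adjusted models add seven confounders: age, gender, where the person lives, severity of intellectual disability, level of risk, autism and clinical comorbidity. For the rest it says: "The secondary outcomes detailed above will be analysed using statistical models analogous to those for the primary outcome". Binary outcomes go to multilevel logistic regression, and secondary outcomes are reported without p values.

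**The concern.** For scales measured at both visits, the plan's direct control for the starting level is the change score. The admissions item is named at follow-up with no baseline partner, so the article describes no such control for it. The covariate list does not make up for this, because earlier admissions are not on it. Admission history is probably the strongest single predictor of later admission.

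The two groups could well differ on it at entry. Table 1 of the article shows that the models differ in referral route, caseload and length of support. Participants come both from existing caseloads and from new referrals. Avoiding unnecessary admission is a stated purpose of ISTs, so readers will look at this contrast. A difference in case mix could then be reported as a difference between service models. The service-level comparison with national data does not fill the gap: the article calls it a proxy and names no period before the study.

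**Working it through.** **1. The passages side by side.**

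| Question | What the article gives |
|---|---|
| When is the admissions item named? | At follow-up; no baseline count named |
| Is there another source for the period before entry? | The baseline CSRI, looking back 6 months; inpatient stays are not mentioned by name |
| Which model applies if admissions are yes/no? | Multilevel logistic regression, which needs no baseline value |
| Which applies if they stay a number? | A model analogous to the primary; form not spelled out |
| Are prior admissions a covariate? | No |

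Under either treatment of the outcome, the adjusted model as described has no term for admissions before entry.

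**2. The plan's own figure.** The stated sample size reproduces. Detecting 0.45 SD at two-sided 5% with 80% power needs 78 per model. Eight ISTs per model give 96/8 = 12 per IST, so the design effect is 1 + (12 − 1) × 0.02 = 1.22. Then 78 × 1.22 = 95.2, rounded up to 96, and 96/0.85 = 112.9, rounded up to 113. The present point does not affect this; 96 per model is used below as the analysed number.

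**3. How large the bias could be.** The article gives no admission rates, so every rate here is an assumption. Let q be the proportion admitted in the 6 months before baseline, p1 the 9-month admission risk for those people and p0 the risk for the rest. Assume no true effect of IST model.

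- Risk in each model = p0 + q × (p1 − p0)
- Spurious odds ratio (OR) = odds in one model ÷ odds in the other
- SE of log OR = √(sum of 1/expected count over the four cells), 96 per model, ignoring clustering and other covariates

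With p1 = 0.30 and p0 = 0.08:

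- q = 0.10: 0.08 + 0.10 × 0.22 = 10.2%
- q = 0.20: 0.08 + 0.20 × 0.22 = 12.4%
- q = 0.30: 0.08 + 0.30 × 0.22 = 14.6%

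| q in the two models | p1 | p0 | Risks | Spurious OR | Bias / SE |
|---|---|---|---|---|---|
| 10% v 20% | 0.30 | 0.08 | 10.2% v 12.4% | 1.25 | 0.48 |
| 10% v 30% | 0.30 | 0.08 | 10.2% v 14.6% | 1.51 | 0.92 |
| 10% v 30% | 0.20 | 0.08 | 9.2% v 11.6% | 1.30 | 0.54 |
| 10% v 30% | 0.40 | 0.05 | 8.5% v 15.5% | 1.97 | 1.47 |
| 15% v 20% | 0.15 | 0.05 | 6.5% v 7.0% | 1.08 | 0.14 |

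The range is about 1.1 to 2.0. It describes a crude contrast. The listed covariates would absorb part of it, by an amount the article gives no means of estimating.

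**4. Cost in parameters.** At 10.2% and 14.6% of 96 there are 9.8 + 14.0 ≈ 24 events. The model effect plus seven covariates takes at least 8 parameters (24/8 = 3.0 events each). Adding prior admission makes at least 9 (24/9 ≈ 2.7).

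**The case against.** A reader might infer that admissions are collected only at follow-up, that the stated model therefore cannot be applied, and that nothing at all is done about case mix. The article supports none of these.

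- The word only does not appear, and the timing phrase may qualify accommodation alone. The baseline CSRI may already hold earlier admissions.
- The logistic rule covers a yes/no outcome without any change score, so a stated model does exist for that version.
- Level of risk, living arrangements and comorbidities are in the adjusted model and are partial proxies for admission history.
- If admissions are kept as a number, the choice of count model is detail that an article can leave to the full analysis plan, which is not shown. It is not part of this point.

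Three further objections bear on the remedy and the size. First, someone already under IST care may have been admitted, or kept out of hospital, because of that IST, so adjusting may remove part of the effect of interest. This stands as a caution. It applies equally to the plan's own change scores, whose baseline is also taken after IST care has begun for such participants. Second, events may be few. That is true, but step 4 shows the adjusted model is already sparse and one more term changes little. Third, the size rests on assumed rates, and no p values are reported. The first part is correct. The second does not remove the problem, because a confounded estimate and interval would still be published.

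The full analysis plan may add an outcome-specific covariate. The article nevertheless publishes a definite confounder list and a rule for secondary outcomes, and this point concerns those.

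**Conclusion.** The point holds in a limited form. As the article is written, the admissions contrast between non-randomised IST models is adjusted for admission history only through partial proxies, although a form completed at baseline probably holds the missing variable. Under assumed rates and no true effect, the crude spurious odds ratio runs from about 1.1 to 2.0, or roughly 0.1 to 1.5 standard errors, before the listed covariates are allowed for. The conclusion assumes that admission history differs between the models at entry, which the article makes plausible but does not show. It concerns a secondary result and leaves the primary analysis and the sample size untouched. It is worth correcting because the outcome matters to the purpose of ISTs and the correction is cheap.

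**What to change.** In the Statistical analysis plan section:

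1. State that admissions between baseline and 9 months are not analysed as a change score.
2. In the adjusted admissions model, add any inpatient admission in the 6 months before baseline, taken from the baseline CSRI, alongside the listed confounders and the random effect of IST. First confirm that the adapted CSRI records inpatient stays. The Economic evaluation plan section suggests so, since it draws health service use outside the IST from that form, but does not say so. If the form does not record them, say that prior admissions could not be adjusted for.
3. Report the unadjusted estimate beside the adjusted one, and describe the adjusted one as the effect from baseline onward, because earlier admissions may partly reflect earlier IST care.

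The cost is a change of wording and one covariate, with no new data or participants if the form holds the item. The downsides are one more parameter in a model that may have few events, and a 6-month look-back set against a 9-month follow-up. The shorter window does not prevent its use as a covariate.

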**Figure 1 F1:**
[figure not shown]
Study participant flow chart.

#### Service-level outcomes

The researchers will collect data from all participating ISTs including the number of people referred; proportion who engage with IST; time to first assessment and delivery of management plan; other IST scope (eg, days of training given) and other engagement with local services (eg, joint assessments with crisis teams) that will provide additional information about the ISTs’ caseload size. We will map our service data onto the reports from the Mental Health and Learning Disabilities Data Set over the study period which provides information on hospital admissions and compares with admissions by IST model. This will provide a proxy measure of IST model impact on admissions.

#### Referrer’s questionnaire

Practitioners from community ID services who frequently refer to ISTs across all sites will be invited to complete a brief questionnaire designed to capture satisfaction with referral processes, reasons for referrals and number of referrals to IST. The questionnaire will be administered either online, via email or post, or a combination of these.

#### Qualitative substudy: stakeholder’s views of ISTs

An embedded qualitative substudy will allow to investigate how IST care is experienced by service users and family carers, and to obtain a multiperspective view of IST functioning within local service contexts, based on user, carer and practitioner views. The researchers will conduct semistructured interviews with (1) IST managers and staff, (2) service users, and (3) family and paid carers. Up to eight service users per IST model, including those who may need support to communicate (provided by family or paid carers); and up to eight carers (a mixture of family and paid) per IST model will be included. The researchers will also attempt to interview a small number of family carers who have recently declined IST contact. Purposive sampling will be employed, in order to include a range of ages, work experience, professional backgrounds, and carer roles and relationships in our sample. In order to gain a broad perspective on IST implementation in England, the researchers will aim to conduct interviews with all managers of the IST services taking part in the phase 2. Interviews with IST managers and staff will be conducted in the early stages of the research study; interviews with service users and family and paid carers will be conducted near the time of discharge from IST services or around the 9-month follow-up, whichever is sooner.

The interview will take place at a location convenient (ie, home, clinic or remotely with the aid of technology) for the participant and will be audio-recorded. Across all stakeholder groups, interview schedules will be designed to explore views and experiences of the role and functioning of ISTs, and how they interface with other health and social care provision within their local context. The semistructured interview schedule will address the operational functioning, benefits and limitations of ISTs, and explore the factors that might affect these following consultation with the patient and public involvement (PPI) representatives. In order to link stakeholder perspectives to specific service contexts, we aim to carry out data collection within seven IST ‘case study’ sites. These sites will be selected from the larger pool of the 16 services, with an aim to include services that vary in terms of team size, caseload size and styles of working based on the reflections and other relevant information available to the research team. Four services will be selected as case studies of ‘independent’ ISTs and three services as case studies of ‘enhanced model’ ISTs. The use of case study sites is appropriate where the research focus is to assess ‘mega systems’ of great complexity.^28^

#### Study termination

The end of the study will be the date of the 9-month follow-up assessment with the study participant. For those who take part in interviews, these will be arranged to take place shortly after the questionnaire completion. Further, if the study failed to recruit adequately, it would be discussed with the study Steering Committee and the funders as to whether it should stop or be extended.

#### Sample size

Based on two IST models, it was estimated that a sample of 96 participants per model (192 in total) would be required to detect a difference of 0.45 SDs in primary outcome score between the two models at the 5% significance level with 80% power and assuming an intraclass correlation of 0.02.^12 29^ After factoring in 15% loss to follow-up, the estimated sample size required increased to 113 participants per model (226 participants in total).

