### Setting and participants

Eight enhanced service provision ISTs and eight independent service provision ISTs (table 1) will be selected at random from ISTs surveyed in phase 1 of the study.^20^ Service users, either already under the care of the 16 ISTs or newly referred, and their caregivers will be identified by IST staff either at first clinical assessment or from the IST services caseloads and asked if they are interested in taking part in the study. Following an expression of interest, the researchers will contact them to provide information about the study and to obtain written or audio-recorded informed consent from those agreeing to undergo further research assessments.

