### Study progress and COVID-19 impact

The first phase of the study has been completed and reported.^20^ The study has faced recruitment challenges which in the main included: reduced capacity to identify sufficient numbers of eligible participants due to small and static caseloads, services withdrawing or changing their remit halfway through the study, inadequate communication between ISTs and Clinical Research Networks which hampered research support. The number of ISTs was expanded to 23, 21 of which contributed participants to the study. The originally estimated 9 months of recruitment were extended to 17 with the last participant enrolled in May 2020; 180 9-month follow-ups have been completed. The last 4 months of recruitment occurred during the coronavirus pandemic and the subsequent lockdown which necessitated changes in study procedures including the introduction of remote completion of the research assessments and qualitative interviews. Those changes were non-substantial amendments (number 7) to the REC that had originally approved the study. Thirteen participants have been lost to follow-up with one death from COVID-19.

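### The stated 80% power allows for clustering but not for the small number of ISTs; with 8+8 ISTs and a between-IST t reference it is about 75%

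*Protocol article*

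**What the plan says.** The Sample size section of the protocol article sets the evaluable number at 96 per model, 192 overall, and describes this number as "required to detect a difference of 0.45 SDs in primary outcome score between the two models at the 5% significance level with 80% power". The clustering input stands in the same sentence: "assuming an intraclass correlation of 0.02". Allowing for 15% loss, this becomes 113 per model, 226 in total.

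Setting and participants plans "Eight enhanced service provision ISTs and eight independent service provision ISTs", chosen at random from the teams surveyed in phase 1. That is 96/8 = 12 analysed participants per IST.

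The article's statistical analysis section estimates the primary comparison from a multilevel linear model of change in ABC score, with IST model as a fixed effect and IST as a random effect. It promises a 95% CI and p value for the primary outcome and does not say which reference distribution they use.

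Study progress and COVID-19 impact later reports: "The number of ISTs was expanded to 23, 21 of which contributed participants to the study". The article gives no power figure for that design.

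**The concern.** Every participant in a given IST has the same exposure, so the information about the model effect lies between ISTs. With 16 ISTs in two groups, the between-IST variance is estimated on 16 - 2 = 14 degrees of freedom. A design effect corrects the size of the standard error but not the uncertainty in estimating it. A formula with normal quantiles treats that standard error as known and therefore gives a power that is too high.

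The comparison is meant to inform commissioning of ISTs. If it shows no clear difference, readers will judge that result against a design said to have an 80% chance of detecting 0.45 SD. If the real figure is lower, the null result is less informative than it appears.

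**Working it through.** **Inputs from the article.** Difference 0.45 SD (SD set to 1); 5% level, taken as two-sided because that reproduces the stated number; 80% power; ICC 0.02; 96 analysed per model; 8+8 ISTs planned; 21 ISTs contributing.

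**Assumptions.** Equal cluster sizes throughout, and a near-even split of the 21 ISTs between models. The article gives neither the split nor the cluster sizes.

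**1. Reproducing the stated figure.**
- Individual sample size: 2 × (1.96 + 0.8416)² / 0.45² = 77.5, so 78 per model.
- Design effect: 1 + (12 - 1) × 0.02 = 1.22.
- 78 × 1.22 = 95.2, so 96 per model; 96 / 0.85 = 112.9, so 113 per model.
- Standard error with 96 per model: √(2 × 1.22 / 96) = 0.1594. Noncentrality: 0.45 / 0.1594 = 2.823.
- Normal-approximation power: Φ(2.823 - 1.96) = 80.6%.

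The stated numbers are therefore reproduced, clustering included.

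**2. Planned design, allowing for 16 clusters.**
- Critical value of t on 14 degrees of freedom: 2.145, against 1.96.
- Noncentral t with 14 degrees of freedom and noncentrality 2.823: power 74.7%. A simulated t test on IST means gives 74.9%.
- For 80% power the noncentrality must be 3.013, so the detectable difference is 3.013 × 0.1594 = 0.480 SD.
- To give a sense of scale, 80% at 0.45 SD on this basis would take 114 analysed per model in 16 ISTs, against 96.

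**3. Sensitivity to the test used (16 ISTs).** A balanced random-intercept model was simulated, fitted by REML with the between-IST variance held at or above zero.

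| Reference | Power | Type I error |
|---|---|---|
| Wald z | about 79% | about 5.4% |
| t, 14 df | about 73% | about 3.6% |

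The z test comes closest to 80% but still falls short, and its type I error is slightly above 5%. The t test on this fit is somewhat conservative because the variance estimate cannot go below zero.

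**4. The 21 contributing ISTs, 192 analysed.**
- Average cluster size: 192 / 21 = 9.14. Design effect: 1 + 8.14 × 0.02 = 1.163.
- Standard error: √(2 × 1.163 / 96) = 0.1556. Noncentrality: 0.45 / 0.1556 = 2.891.
- The article's own normal formula: 82.4%.
- Noncentral t with 19 degrees of freedom: 78.3%; detectable difference with 80% power about 0.46 SD.
- Simulated REML with Wald z: 80.6%, type I error about 5.1%.

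With the 180 follow-ups reported as completed at the time of writing, the t(19) figure is 76.1%.

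**The case against.** Four points can be made for the plan.

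**The arithmetic is correct.** A reader might infer that the calculation ignored clustering or the 16 services. It did not: 96 is reached only with the ICC of 0.02 and 12 participants per IST. This stands. What is missing is the small-cluster correction alone.

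**The 75% depends on the reference distribution.** The article does not fix it and refers to a separate analysis plan that is not shown. The degrees-of-freedom method may be specified there, so its absence from the article is not a fault. This also stands. It does not rescue the 80%, however: with 16 ISTs none of the small-cluster calculations above reaches 80%, and the closest of them has type I error slightly above 5%.

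**The expansion helps.** A reader might take the unrevised figure as a second defect, made worse by the move to 21 ISTs. The numbers do not support that. At the same total, more and smaller clusters raise power, and with a z reference the stated 80% is recovered at close to the nominal level. The sample size text reports a prospective estimate, and the expansion is disclosed openly elsewhere in the article.

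**The gap is modest.** The detectable difference moves from 0.45 to 0.48 SD, or to 0.46 SD with 21 ISTs, and the result will be reported with a 95% CI. This limits how much the point matters, but the article still states a power that the planned design does not have.

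**Conclusion.** The point holds in limited form. The 80% rests on a normal approximation with a design effect and makes no allowance for having only 16 clusters. For the planned 8+8 ISTs with 192 analysed, power at 0.45 SD is about 75% with a between-IST t reference, a shortfall of about 5 percentage points. A Wald z test leaves it about 1 point short, with slight type I inflation. For the 21 contributing ISTs the shortfall is about 2 points with t and none with z.

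These figures take the article's ICC of 0.02 as given and rest on the equal cluster sizes and near-even split assumed above. Unequal cluster sizes would lower them. They describe a stated power that is somewhat too favourable; they do not show an arithmetic slip, an omission of clustering or a fault in the expansion.

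**What to change.** Restate the planned power as about 75% for 8+8 ISTs at 0.45 SD, and add that it is about 78% for the 21 contributing ISTs at 192 analysed. Update the second figure with the actual split by model, the cluster sizes and the number analysed.

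Base the primary 95% CI and p value on a small-sample degrees-of-freedom method, such as REML with Kenward-Roger or Satterthwaite, if the SAP does not already do so.

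No extra participants are needed. The cost is a few sentences and a slightly less favourable stated power.
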